The sample size was determined using institutional retrospective data supported by published clinical literature. A preliminary analysis of 20 patients undergoing ileostomy formation in 2024 at the University Clinical Center in Gdańsk demonstrated a mean POD 1–3 output of 1160 mL/day (SD = 360 mL), with 17 complete datasets available. To account for uncertainty inherent to small preliminary samples, the standard deviation was conservatively inflated to 400 mL for planning purposes. Under these assumptions and using a two-sided t-test (α = 0.05, power = 80%), the estimated sample size was 41 participants per arm. After accounting for an anticipated 15% dropout rate, the required enrollment increased to 49 participants per arm (n = 98 total). To minimize the risk of underpowering due to variance misestimation, target enrollment was increased to 50 participants per arm (n = 100 total). Sensitivity analyses demonstrated preservation of 80% power for SD values up to 415 mL. With 50 participants per arm, statistical power remains 87.5% assuming SD = 400 mL and ≥83% for SD ≤ 425 mL, indicating robustness to moderate deviations from planning assumptions. The assumed 15% attrition rate is supported by institutional experience from comparable perioperative trials. Analyses will follow a modified intention-to-treat principle, with all exclusions transparently documented to limit attrition bias. Variance assumptions will be reassessed at a preplanned interim analysis focused solely on variability estimation; if observed dispersion materially exceeds projections, mitigation strategies such as extended recruitment will be considered without evaluation of treatment effect, thereby preserving statistical validity.

No randomized trial has established a validated minimal clinically important difference for postoperative ileostomy output. Therefore, the calculation was anchored to clinically meaningful output thresholds used in routine practice to define high-output stoma, commonly defined as output exceeding 1.4 L/24 h and associated with clinically significant fluid and electrolyte disturbances requiring medical intervention [30]. As stoma output represents an objective and routinely recorded parameter, the primary endpoint is considered minimally susceptible to assessment bias despite the open-label design.

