In the institutional cohort, a reduction of 250 mL/day corresponds to 20–25% of typical POD 1–3 output volumes and is sufficient to shift a substantial proportion of patients below commonly applied high-output thresholds, which trigger intensified monitoring and therapeutic escalation in routine care. The selected effect size, therefore, reflects a clinically actionable and patient-relevant improvement rather than a purely statistical difference.

Interim analysis:

An interim analysis will be performed after 20 patients total (10 per arm) have completed postoperative days 1–3 assessment and have primary outcome data available. This interim timepoint corresponds to approximately 25% of the target enrollment. This analysis will assess feasibility, safety, and conditional power. A Haybittle–Peto boundary will be applied for early stopping due to efficacy (*p* < 0.001, two-sided) [31], while recruitment may be discontinued for futility if conditional power to detect the prespecified 250 mL/day difference falls below 20%. As futility stopping may increase the risk of type II error, any decision to discontinue recruitment will be interpreted cautiously and will considerconsistency of observed trends together with clinical plausibility rather than conditional power alone.

The interim review is primarily safety-focused and will be conducted by an independent statistician not involved in trial conduct. Given the modest sample size and the well-established perioperative safety profile of proton pump inhibitors, rigid numerical stopping thresholds for infrequent adverse events are not prespecified. Instead, the review will include descriptive assessment of serious adverse events, clinically relevant electrolyte disturbances (including hypomagnesemia, hyponatremia, and hypokalemia), acute kidney injury, and any unexpected safety signals potentially related to intensified omeprazole therapy. Any clinically meaningful imbalance in serious or treatment-related adverse events may prompt trial modification, temporary suspension, or early termination in accordance with Good Clinical Practice and institutional safety oversight procedures. Interim results will remain confidential and will not be disseminated as a standalone report.

Statistical analyses:

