The study is adequately powered for a physiological endpoint, whereas secondary outcomes—including HOS incidence, dehydration-related complications, and 30-day readmissions—are analysed exploratorily; observed associations should therefore be considered hypothesis-generating pending confirmation in adequately powered trials. Conduct within two academic centers may also influence generalizability where postoperative pathways differ, despite standardized guideline-based management.

Given that both groups receive perioperative PPI prophylaxis as part of standard care and short-term intensified dosing has not been associated with a materially increased risk of serious adverse events, safety monitoring in STOP-HOS-1 prioritizes the detection of unexpected or imbalanced adverse events rather than predefined numerical stopping thresholds for rare complications [26].

Positive findings would be readily implementable and could strengthen the evidentiary basis for HOS management algorithms that currently rely largely on physiologic reasoning and lower-grade evidence. Conversely, neutral results would be equally informative, prompting the reconsideration of routine PPI escalation in early postoperative ileostomy care and redirecting attention toward alternative or combined strategies, including optimized oral rehydration, structured antimotility pathways, or phenotype-targeted treatment approaches such as biologically defined “net secretor” populations. In sum, STOP-HOS-1 directly tests an intuitive, low-cost, and scalable intervention embedded in routine postoperative care. By anchoring decision-making to quantitative effluent outcomes and clinically relevant complications, the trial aims to generate evidence capable of either reinforcing current practice where justified or recalibrating it where benefit is not supported by high-quality data.

Trial Status: The first version of the protocol was registered at ClinicalTrials.gov (NCT06917963) on 5 April 2025. Recruitment started on 10 April 2025 and is expected to conclude by July 2027.

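### The 87.5% and ≥83% power figures assume that nobody is lost; with the planned 15% attrition, power is about 81–83% at SD 400 and 76–78% at SD 425

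*Protocol article*

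**What the plan says.** All the figures are in the protocol article, section 3 (Analysis), under Sample size calculation.

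- **Pilot data.** The local cohort "demonstrated a mean POD 1–3 output of 1160 mL/day (SD = 360 mL), with 17 complete datasets available".
- **Planning SD.** From there, "the standard deviation was conservatively inflated to 400 mL for planning purposes".
- **Evaluable number.** The calculation is described as "using a two-sided t-test (α = 0.05, power = 80%), the estimated sample size was 41 participants per arm". The difference to be detected is 250 mL/day, as given under Endpoints and Interim analysis.
- **Attrition.** "After accounting for an anticipated 15% dropout rate, the required enrollment increased to 49 participants per arm". Enrolment is then raised to 50 per arm, and this last step is presented as protection against a larger SD than planned.
- **Tolerance, first sentence.** "Sensitivity analyses demonstrated preservation of 80% power for SD values up to 415 mL". No sample size is attached.
- **Tolerance, second sentence.** "With 50 participants per arm, statistical power remains 87.5% assuming SD = 400 mL and ≥83% for SD ≤ 425 mL". The plan concludes from this that the design withstands moderate departures from its assumptions.

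Under Statistical analyses and Handling of missing data, the primary set is limited to participants whose ileostomy was formed as planned and who have output on at least two of the three days. Those with two or more missing days are left out.

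**The concern.** Fifty per arm is the enrolled number, already inflated to absorb a 15% loss. Quoting power at 50 uses the attrition allowance a second time, as if it were spare sample size. The same paragraph treats the 15% loss as realistic, and the primary analysis set is defined so that participants without enough output data leave it.

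What is at stake is the reading of the robustness statement. A reader sees at least 83% power at SD 425 and concludes that an SD somewhat above 400 does no harm. If power there is in fact below 80%, that conclusion is wrong. The planned interim reassessment of variability would also be judged against an over-favourable reference.

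**Working it through.** **Inputs** (all from the protocol article): two-sided α = 0.05; difference 250 mL/day; SD 400, with 415 and 425 as the stated sensitivity values; 1:1 allocation; 15% loss; 50 enrolled per arm.

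**Formulas.** Normal approximation: power = Φ(250 / (SD·√(2/n)) − 1.960). The exact version is the two-sample t-test power from the noncentral t distribution with 2n − 2 degrees of freedom. Both are shown because the plan names a t-test, while its n of 41 matches the normal approximation.

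**Step 1: reproduce the sample size.**
- n = 2·(1.960 + 0.842)²·400²/250² ≈ 40.2, so 41 per arm. The exact t-test gives 79.8% at 41 and 80.8% at 42.
- 41/0.85 = 48.2, so 49 per arm. The plan's 41 and 49 both reproduce.

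**Step 2: reproduce the stated power at n = 50.**
- SD 400: 250/(400 × 0.2) = 3.125, and Φ(1.165) = 87.8%. Exact t: 87.2%. Stated: 87.5%.
- SD 425: 250/(425 × 0.2) = 2.941, and Φ(0.981) = 83.7%. Exact t: 82.95%. Stated: at least 83%.

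The stated figures are therefore the power with all 50 enrolled per arm analysed.

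**Step 3: apply the plan's own attrition.** 50 × 0.85 = 42.5, so 42–43 evaluable per arm.

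| SD | Exact t, n = 42–43 | Normal, n = 42–43 | Stated |
|---|---|---|---|
| 360 | 88.2–88.9% | 88.9–89.6% | – |
| 400 | 80.8–81.7% | 81.7–82.6% | 87.5% |
| 415 | 77.9–78.9% | 78.8–79.8% | 80% (n not given) |
| 425 | 75.9–76.9% | 76.9–77.9% | ≥83% |

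**Step 4: largest SD that keeps 80% power.** Under the normal approximation this is 250/(2.802·√(2/n)).

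| n per arm | Exact t | Normal |
|---|---|---|
| 42 | 404 | 409 |
| 43 | 409 | 414 |
| 50 | 442 | 446 |

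The stated 415 lies next to the 43-per-arm normal value and far from the 50-per-arm values. It looks like a post-attrition figure, although the plan does not say so.

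**Step 5: how little loss the SD 425 claim allows.** To keep even 80% power at SD 425, 46 (normal) or 47 (exact t) per arm must be analysed. That is a loss of at most 4/50 = 8% or 3/50 = 6%, against the 15% planned.

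**Step 6: the step from 49 to 50.** One more enrolled participant per arm adds 1 × 0.85 = 0.85 evaluable.

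**The case against.** Several points on the other side stand, and they limit how far the criticism goes.

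- **The figures are not miscalculated.** 41, 49, 87.5% and 83% all reproduce, and the second sentence states its condition of 50 per arm openly. The fault is the choice of denominator.
- **A reader might infer that the SD 415 tolerance cannot be reproduced.** The documents do not support that. At 43 per arm, power at SD 415 is 79.8% by the normal approximation. What is missing is the n.
- **A reader might infer that the two tolerance sentences contradict each other.** Only the second is tied to 50 per arm. On about 43 and on 50 per arm, both can be roughly true. They need labels.
- **A reader might infer that the trial has no reserve, or that "The study is adequately powered for a physiological endpoint" in the Discussion is wrong.** That goes too far. SD 400 is already raised from the pilot 360, at which post-attrition power is about 88–90%. The 80% target is met at SD 400. The plan also reassesses variability at an interim and allows longer recruitment.
- **Not every dropout need leave the primary set.** Participants with one missing day are kept, and multiple imputation is planned. The analysed number may lie between 42 and 50, which puts exact-t power between about 81% and 87% at SD 400, and between about 76% and 83% at SD 425.

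The last point softens the size of the gap but does not rescue the sentence. The upper end needs no loss at all, and the plan itself treats 15% as the expected figure when it sets enrolment.

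**Conclusion.** The point holds in a limited form. The 87.5% and ≥83% figures are no-attrition values, quoted as evidence of robustness in a paragraph that plans for 15% attrition. On 42–43 evaluable per arm, power is about 81–83% at SD 400 (roughly 5 to 7 points below the stated value). At SD 425 it is about 76–78%, at least 5 points below the stated minimum and under the 80% target. The design keeps 80% power up to an SD of about 404–414, not beyond 425.

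This rests on a true difference of 250 mL/day, equal SDs in the two arms, and the full 15% loss leaving the primary analysis. With smaller losses the shortfall shrinks, as shown above. An SD of 425 is not remote: if the pilot SD of 360 comes from the 17 complete datasets and the data are roughly normal, its 95% confidence interval is √(16 × 360²/28.85) to √(16 × 360²/6.91), or 268 to 548.

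The statement is wrong as written, but the design, the test and the enrolment target are not put in question.

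**What to change.** In the Sample size calculation paragraph:

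1. Give power on the expected evaluable number: 42–43 per arm after 15% loss, about 81–83% at SD 400 and about 76–78% at SD 425, with 80% kept up to an SD of about 404–414. It is better to choose one formula and say which. For the t-test that the plan names, the values are 80.8–81.7%, 75.9–76.9% and 404–409.
2. If 87.5% and 83% are kept, label them as the case with no attrition.
3. State the n and formula behind the SD 415 tolerance, or replace it with the limit from item 1.
4. Soften the claim that going from 49 to 50 per arm protects against a larger SD, since it adds less than one evaluable participant per arm. The real allowance is the increase of the planning SD from 360 to 400, together with the interim variance check.
5. Reword the robustness conclusion to match.

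Enrolment stays at 100 and no trial procedure changes. The cost is one reworded paragraph with less favourable figures.

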## Abstract

Introduction: High-output stoma (HOS) is a frequent and morbid complication following ileostomy formation. Proton pump inhibitors (PPIs) may reduce intestinal secretions, but no randomized trial has yet tested whether intensified intravenous omeprazole treatment prevents or mitigates early postoperative HOS. We aim to determine whether intensified PPI dosing reduces early postoperative ileostomy output compared with standard dosing. Methods and Analysis: STOP-HOS-1 is a randomized, parallel-group, open-label, superiority trial conducted at two academic centers in Poland. The target sample size is 100 adults undergoing the formation of a loop or end ileostomy. Participants will be randomized 1:1 to receive either: intensified omeprazole group—80 mg IV loading dose, followed by 40 mg IV twice daily through postoperative day (POD) 10, or standard omeprazole group—40 mg IV once daily through POD 10. The primary outcome is mean ileostomy output (mL/24 h) across POD 1–3. A ≥250 mL/day reduction is prespecified as clinically meaningful. Key secondary outcomes include: incidence of HOS (≥1000 mL/day for ≥3 consecutive days or ≥1400 mL on any single day), time to output stabilization (<1400 mL/day for 3 consecutive days), dehydration-related complications (hyponatremia, hypokalemia, acute kidney injury), length of hospital stay and 30-day readmission rate. The primary analysis will follow the intention-to-treat principle. One interim safety analysis is planned after enrollment of the first 20 patients. Discussion: Although PPIs are commonly used to reduce ileostomy output, high-quality evidence in the early postoperative setting is lacking. STOP-HOS-1 targets the critical period when output is most variable, and complications are most frequent, using a pragmatic randomized design and an objective, clinically meaningful primary endpoint. Conclusions: STOP-HOS-1 will provide the first randomized evidence on whether intensified postoperative PPI therapy reduces early ileostomy output and HOS-related morbidity, informing future standards of care.

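### The protocol describes an interim with no evaluation of treatment effect, but the only interim it sizes has efficacy and futility rules that need that effect, and the futility rule serves little purpose at 10 per arm

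*Protocol article*

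**What the plan says.** All of the following is in the protocol article.

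- **Abstract:** "One interim safety analysis is planned after enrollment of the first 20 patients".
- **3. Analysis, sample size calculation:** "Variance assumptions will be reassessed at a preplanned interim analysis focused solely on variability estimation". If dispersion is larger than planned, mitigation such as extended recruitment "will be considered without evaluation of treatment effect, thereby preserving statistical validity". No sample size or date is attached to this look.
- **3. Analysis, interim analysis:** the look takes place when 20 patients (10 per arm) have completed POD 1–3 and have primary outcome data. Its stated purposes are feasibility, safety and conditional power. "A Haybittle–Peto boundary will be applied for early stopping due to efficacy" (p<0.001, two-sided), and "recruitment may be discontinued for futility if conditional power to detect the prespecified 250 mL/day difference falls below 20" per cent. The section adds that a futility decision will not rest on conditional power alone, that the review is mainly about safety, that an independent statistician conducts it, and that results stay confidential.
- **Same section, on timing:** "This interim timepoint corresponds to approximately 25% of the target enrollment". The target is 100.

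**The concern.** An efficacy p-value and a conditional power both require the between-arm difference in the primary outcome. A look that computes them evaluates the treatment effect. If the variability look and the 20-patient look are the same, the sample size text misdescribes it, and the reason given there for preserved validity does not apply. If they are two looks, the protocol does not say so, and the variance check has no size or timing.

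The futility rule also leaves open which effect is projected for the patients still to come: the planned 250 mL/day or the trend seen so far. With only 10 per arm this choice decides how the rule behaves. The statistician running the look needs one unambiguous instruction, and the stated power takes no account of the rule.

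**Working it through.** **Inputs.** Effect 250 mL/day; SD 400 mL ("the standard deviation was conservatively inflated to 400 mL for planning purposes"); two-sided α 0.05; 10 per arm at the interim; 41 per arm (evaluable sample) to 50 per arm (full target) at the end. Assumptions: normal outcomes and equal SDs.

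**1. The plan's own figures.** The protocol states "using a two-sided t-test (α = 0.05, power = 80%), the estimated sample size was 41 participants per arm". The normal formula gives 41 per arm, and the t-based solution is 41.2. Dropout: 41/0.85 = 48.2, so 49. Power at 50 per arm and SD 400 is 87.2% (t-test) to 87.8% (normal), against the stated 87.5%. The planning figures reproduce.

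**2. Interim fraction.** 20/100 = 20%. Only against 2 × 41 = 82 evaluable patients is it 20/82 = 24.4%.

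**3. Conditional power.** With t = 10/n and interim statistic Z,

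CP = Φ{[Z√t + θ(1 − t) − 1.96]/√(1 − t)}.

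CP is below 20% when Z√t + θ(1 − t) < k, where k = 1.96 − 0.8416√(1 − t). The interim standard error is 400 × √(2/10) = 178.9 mL.

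- n = 50: t = 0.200, k = 1.207, planned drift θ = 250/(400√(2/50)) = 3.125.
- n = 41: t = 0.244, k = 1.228, θ = 250/(400√(2/41)) = 2.830.

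*Projecting the planned 250 mL/day:* cut-off Z = [k − θ(1 − t)]/√t.

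- n = 50: (1.207 − 2.500)/0.447 = −2.89; × 178.9 = −517 mL/day.
- n = 41: (1.228 − 2.140)/0.494 = −1.85; × 178.9 = −330 mL/day.

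*Projecting the observed trend:* θ = Z/√t, so the cut-off is Z = k√t.

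- n = 50: 1.207 × 0.447 = 0.540; × 178.9 = 97 mL/day.
- n = 41: 1.228 × 0.494 = 0.607; × 178.9 = 109 mL/day.

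**4. Chance of crossing.** This is Φ(cut-off) under no effect and Φ(cut-off − 1.398) under a true 250 mL/day, since 250/178.9 = 1.398.

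| Projection | Final n per arm | Triggers when observed reduction is below | No effect | True 250 |
|---|---|---|---|---|
| Planned 250 | 50 | −517 mL/day | 0.2% | 0.001% |
| Planned 250 | 41 | −330 mL/day | 3.2% | 0.06% |
| Observed trend | 50 | 97 mL/day | 70.5% | 19.6% |
| Observed trend | 41 | 109 mL/day | 72.8% | 21.4% |

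Under the planned-effect projection, an observed difference of exactly zero still leaves conditional power at 73% (n = 50) or 58% (n = 41). For SD 360–425, the observed-trend crossing rate under a true 250 runs from 15.6% to 23.9%. The planned-effect crossing rate runs from 0.02% to 5.6% under no effect and stays below 0.2% under a true 250.

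**5. Power if the observed-trend rule were always obeyed** (400,000 simulated trials, t-tests): 87.2% falls to 73.2% at 50 per arm (14.0 points), and 79.9% to 67.4% at 41 per arm (12.5 points). Under the planned-effect projection the loss is nil to within 0.1 point.

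**6. Efficacy boundary.** p<0.001 on 18 df needs |t| > 3.92, that is 3.92 × 178.9 ≈ 702 mL/day. Under the planned effect it is crossed about 1.8% of the time.

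**The case against.** Several stronger readings are tempting, and the documents do not support them.

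- *Three incompatible interims.* A reader might set the abstract's safety label against the interim section as well. A safety-led look can carry stopping rules, so the two are compatible. Only the trigger differs slightly (enrolment against completed POD 1–3 data). The substantive conflict is between the sample size text and the interim text.
- *Two separate looks.* The variance check has no stated size, and the abstract's single interim safety analysis does not strictly exclude a second look of another kind. This is possible, but the protocol describes no second look. For the same reason, criticism of how precisely an SD can be estimated from 20 patients does not hold: that number is never attached to the variance check.
- *A one-in-five chance of wrongly stopping.* This needs the observed-trend projection and automatic obedience. The wording, which refers to detecting the prespecified difference, leans towards the planned effect, and the rule is expressly non-binding. The protocol itself acknowledges the type II risk.
- *Lost type I error control.* None is shown. A look at p<0.001 can add at most 0.001 to the error rate, and futility stopping cannot raise it. Confidential handling by an independent statistician also limits leakage.
- *A defective Haybittle–Peto boundary.* It is meant to be almost uncrossable early. A 1.8% chance of use is conservative and is not an error.

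It can also be said that the projected effect is a detail for the analysis plan. That is fair for the missing assumption taken alone. It does not answer the contradictory statements about whether the effect is evaluated, which a separate document cannot make consistent. Nor does it change the finding that neither projection makes the rule useful at this size.

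**Conclusion.** The point holds in a limited form. The statement that the interim makes no evaluation of treatment effect cannot stand for the 20-patient look, and 25% of target enrolment should read 20%. Both are wrong as written.

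At 10 per arm the conditional-power rule adds little or does harm. On the favoured reading it stops 0.2–3.2% of trials with no effect and under 0.1% of trials with a true 250 mL/day effect. On the other reading it is crossed in about 20% of trials with that effect, with a power loss of about 13–14 points as an upper bound. These figures assume SD 400 mL, 41–50 per arm at the end and a final two-sided test at 0.05. The planned sample size and power are not in question here.

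**What to change.** 1. State whether there is one interim look or two, with the size and timing of each, and align the abstract, the sample size text and the interim text.
2. Make the variance check a blinded check of the pooled SD, separate from any look that uses the between-arm difference. Restrict the no-evaluation statement to that check.
3. Drop the conditional-power futility rule at 20 patients and keep that look for safety and feasibility. If the rule is kept, name the projected effect and state what the rule does to power.
4. The Haybittle–Peto boundary may stay or go. If it stays, the sample size text must not say that the same look makes no evaluation of treatment effect.
5. Correct 25% to 20% of target enrolment, or give 24.4% of the 82 evaluable patients as the stated denominator.

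The cost is wording, with no change in sample size. The small downside is the loss of a futility stop that is almost never used, or is unreliable, at this size. Recruitment started in April 2025, so the 20-patient look may already have taken place. If so, the amendment should record what was computed and who saw it.
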